## List of Abbreviations

|      |                                         |
|------|-----------------------------------------|
| Tdap | Tetanus diphtheria, acellular pertussis |
| RCT  | Randomised controlled trial             |
| KK   | Klinik Kesihatan                        |
|      |                                         |
|      |                                         |
|      |                                         |

## Research Synopsis

|                          |                                                                                                                                                                                                                                                                                                                                                                                                                                                                                                                                                                                                                                                                                                                                                              |
|--------------------------|--------------------------------------------------------------------------------------------------------------------------------------------------------------------------------------------------------------------------------------------------------------------------------------------------------------------------------------------------------------------------------------------------------------------------------------------------------------------------------------------------------------------------------------------------------------------------------------------------------------------------------------------------------------------------------------------------------------------------------------------------------------|
| Study title              | Effectiveness of the Influenza and Tdap Vaccination Educational and Learning Module (Introduce-Programme) in Improving Knowledge and Future Uptake of Vaccination among Pregnant Mothers in Primary Care Clinics: A Randomised Control Trial                                                                                                                                                                                                                                                                                                                                                                                                                                                                                                                 |
| Study Population         | All pregnant women attending Klinik Kesihatan Kajang, Klinik Kesihatan Bangi, Klinik Kesihatan Batu 9, and Klinik Kesihatan Balakong during the period of 1 st May 2025- 30 th April 2026                                                                                                                                                                                                                                                                                                                                                                                                                                                                                                                                              |
| Study Design             | A randomised controlled trial (RCT) will be conducted in four primary care clinics in Hulu Langat district which are Klinik Kesihatan Kajang, Klinik Kesihatan Bangi, Klinik Kesihatan Batu 9 and Klinik Kesihatan Balakong. The study duration is 12 months, with recruitment over 6 months. A second follow-up will be conducted one month after providing the InTroDuce-Programme. Two clinics will be randomly assigned to administer the InTroDuce-Programme, while the other two will be provided with standard care, in order to minimise contamination.                                                                                                                                                                                              |
| General Objective        | To evaluate the effectiveness of the InTroDuce-Programme in improving knowledge and future uptake of influenza and Tdap vaccination among pregnant mothers.                                                                                                                                                                                                                                                                                                                                                                                                                                                                                                                                                                                                  |
| Specific Objectives      | 
 
1) To determine the sociodemographic factors and clinical variables among study population.
 
2) To determine the prevalence of future vaccination uptake following the InTroDuce-Programme.
 
3) To evaluate the level of participants' attitudes and barriers towards future vaccination uptake before and after the InTroDuce-Programme.
 
4) To determine the effectiveness of the InTroDuce-Programme in improving knowledge and future uptake of influenza and Tdap vaccination among pregnant mothers.
 
5) To determine the factors associated with low future uptake of vaccine with socio-demographic factors (age, race, income, education) among pregnant mothers.
 
 |
| Study endpoints/outcomes | 
Primary Outcome: Improvement in participants' knowledge of vaccination safety, benefits, and future uptake intentions.
 
Secondary Outcomes: Identification of barriers to vaccination uptake and socio-demographic factors influencing outcomes.
                                                                                                                                                                                                                                                                                                                                                                                                                                                                                  |

|                |                                                  |
|----------------|--------------------------------------------------|
|                |                                                  |
| Sample Size    | 351 participants                                 |
| Study Duration | 1st October 2024- 31 st December 2026 |

## **1.0 Background and Significance**

Vaccination during pregnancy is a crucial public health measure that prevent both the mother and her expectant child from getting severe infectious diseases such as influenza and pertussis (1). However, despite strong evidence supporting their safety and effectiveness, vaccination rates towards influenza (2), pertussis (3) during pregnancy remain suboptimal globally. This gap in preventive care is exacerbated in middle income country like Malaysia and presents a significant public health challenge that requires innovative, evidence-based solutions. Addressing this gap is particularly important as pregnant women face heightened vulnerability to respiratory infections due to physiological and immunological changes during pregnancy. Recent systematic reviews indicate that pregnant women are approximately four times more likely to be hospitalized with influenza compared to non-pregnant women (4).

The incidence of influenza, adjusted for the population of women of childbearing age in middle-income countries were 88.7 cases per 10,000 pregnant woman-months during the influenza season(5) . Complications can be severe, including increased risks of hospitalization, late pregnancy loss, and reduced infant birthweight (5). Furthermore, maternal infection with respiratory viruses has been associated with adverse pregnancy outcomes, including preterm birth and fetal growth restriction (6). Similarly, pertussis poses a substantial threat to infants under two months of age, who experience the highest rates of hospitalization and death before completing their primary vaccination schedule (7).

In Malaysia, the Ministry of Health Malaysia has issued recommendations for routine influenza and tetanus-diphtheria-acellular pertussis (Tdap) vaccination during pregnancy to mitigate the risks (8). Despite these vaccines have demonstrated robust safety profiles and effectiveness in protecting both mother and infant (9,10), the low vaccination uptake has been reported due to the presence of multiple barriers such as vaccine safety, inadequate provider recommendations, limited access to vaccination services, and socioeconomic disparities (11). Studies have shown that these barriers are particularly pronounced among socioeconomically disadvantaged populations (12).

Digital educational interventions have emerged a promising tool to address vaccine hesitancy and increase uptake rates. A systematic review reported that digital interventions using video appeared more effective than text messages in effectively deliver health information for behavioral changes (13).

Leveraging these findings, the Influenza and Tdap Vaccination Educational and Learning Module (InTroDuce-Programme) was developed as a comprehensive, web-based educational intervention to provide vaccine related information and to address concerns in order to improve maternal vaccination uptake in Malaysia. This research is particularly timely and relevant given the ongoing global emphasis on vaccine-preventable diseases and the need for evidence-based interventions to improve maternal vaccination rates in middle-income countries. By targeting pregnant women through digital-based education module, this intervention aims to improve maternal knowledge, address safety concerns and ultimately improving

maternal uptake vaccination rates in Malaysia.

## **2.0 Objective**

**General objective:** To evaluate the effectiveness of the InTroDuce-Programme in improving knowledge and future uptake of influenza and Tdap vaccination among pregnant mothers.

### **Specific objectives:**

- 1) To determine the sociodemographic factors and clinical variables among study population.
- 2) To determine the prevalence of future vaccination uptake following the InTroDuce-Programme.
- 3) To evaluate the level of participants' attitudes and barriers towards future vaccination uptake before and after the InTroDuce-Programme.
- 4) To determine the effectiveness of the InTroDuce-Programme in improving knowledge and future uptake of influenza and Tdap vaccination among pregnant mothers.
- 5) To determine the factors associated with low future uptake of vaccine with socio-demographic factors (age, race, income, education) among pregnant mothers.

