## Cluster definition based on urban and suburban classification

Klinik Kesihatan Kajang and Klinik Kesihatan Bangi are classified as urban, while Klinik Kesihatan Batu 9 and Klinik Kesihatan Balakong are classified as suburban. These clinics were selected due to their geographic and demographic similarity, coupled with variability in socioeconomic, educational, cultural, and attitudinal factors. This selection ensures a balanced representation of diverse populations, enhancing the generalizability and applicability of the study findings. The approach is particularly valuable for comprehensively understanding the factors that influence vaccine knowledge and uptake among pregnant mothers.

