## Random Allocation of Clinics

- **Random Assignment:** One clinic from each category (urban and suburban) will be randomly assigned to either the intervention or control group using an online random number generator. This method ensures unbiased allocation and maintains the balance of geographic representation in both groups.
  - **Intervention Clinic:** The clinics will receive the **InTroDuce Programme**, where pregnant women attending the clinic will undergo the educational module on influenza and Tdap vaccination.
  - **Control Clinic:** The clinics will serve as the control group, where pregnant women will receive the standard antenatal care.

**The rationale for Randomization is to minimise contamination.** Randomizing at the clinic level (cluster randomization) rather than at the individual level will help reduce the risk of contamination, where participants in the same clinic may share information or influence each other's behaviour. By assigning entire clinics to either intervention or control, the study ensures that participants within each clinic receive consistent and isolated exposure to the educational materials or standard care.

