### 3.4 Sample Size

The sample size was calculated using openEpi software based on earlier study which demonstrated proportion of 55% in intervention group (website with vaccine information) and 36% in control group (usual care) (14) The final sample size is 351 based on the design effect of 1.3, 20% of non-response rate, 95% CI, 80% of power and significant value of 0.05.

| Examples                                 | Sample Size: X-Sectional, Cohort, & Randomized Clinical Trials |        |                |
|------------------------------------------|---------------------------------------------------------------------------|--------|----------------|
| Help                                     |                                                                           |        |                |
| Two-sided significance level(1-alpha):   |                                                                           |        | 95             |
| Power(1-beta, % chance of detecting):    |                                                                           |        | 80             |
| Ratio of sample size, Unexposed/Exposed: |                                                                           |        | 1              |
| Percent of Unexposed with Outcome:       |                                                                           |        | 36             |
| Percent of Exposed with Outcome:         |                                                                           |        | 55             |
| Odds Ratio:                              |                                                                           |        | 2.2            |
| Risk/Prevalence Ratio:                   |                                                                           |        | 1.5            |
| Risk/Prevalence difference:              |                                                                           |        | 19             |
|                                          | Kelsey                                                                    | Fleiss | Fleiss with CC |
| Sample Size - Exposed                    | 109                                                                       | 108    | 118            |
| Sample Size-Nonexposed                   | 109                                                                       | 108    | 118            |

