### **3.9 Statistical Analysis Plan**

#### **Statistical Methods:**

- a. Primary outcome (knowledge score) will be analyzed using paired t-tests or Mann-Whitney U tests for non-parametric data.
- b. Secondary outcomes (vaccination uptake which is yes or no) will be analyzed using multiple logistic regression to determine the factors associated with no vaccination uptake intention.

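### The objective 5 regression names no clinic or arm term, so pooled odds ratios for income and education can partly reflect differences between clinics or arms

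*Protocol*

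**What the plan says.** The fifth specific objective (Protocol 2.0) is "To determine the factors associated with low future uptake of vaccine with socio-demographic factors (age, race, income, education) among pregnant mothers". Section 3.5, Phase 3, also lists socio-demographic influences on outcomes among the secondary outcomes.

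The analysis is in 3.9(b): yes/no uptake "will be analyzed using multiple logistic regression to determine the factors associated with no vaccination uptake intention". No covariates are listed. Clinic, urban/suburban stratum, arm and clustering are not mentioned.

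On the clinics, 3.1 (Cluster definition) says that "Klinik Kesihatan Kajang and Klinik Kesihatan Bangi are classified as urban, while Klinik Kesihatan Batu 9 and Klinik Kesihatan Balakong are classified as suburban", and that they were "selected due to their geographic and demographic similarity, coupled with variability in socioeconomic, educational, cultural, and attitudinal factors". Under Random Allocation of Clinics, one clinic of each type goes to each arm: "Randomizing at the clinic level (cluster randomization) rather than at the individual level will help reduce the risk of contamination".

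Section 3.4 plans on 55% with the outcome in the intervention group and 36% under usual care, with a design effect of 1.3. Clustering is thus recognised in the design and the sample size, but not in the stated model.

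**The concern.** A pooled logistic coefficient for income combines two contrasts: lower- against higher-income women within a clinic, and clinics with many low-income attenders against clinics with few. The two agree only if clinics with different income mixes would otherwise have the same level of intention. The Protocol gives reason to doubt that. It describes the clinics as varied in socioeconomic and educational factors, which are exposures in objective 5, and in attitude, which bears on intention. Section 1.0 also names provider recommendation and access as barriers, and both can differ by clinic.

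Arm is a second route. It is fixed by clinic, it is expected to shift intention, and there are only two clinics per arm. If the intervention clinics have a different income mix from the control clinics, an arm difference can look like an income effect.

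Objective 5 asks which women have low intention. A pooled odds ratio could point to low-income or less-educated women when the difference lies between clinics or arms, which would call for a different response.

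**Working it through.** **1. The plan's own figures.** Fleiss without continuity correction, two-sided 0.05, 80% power, 55% v 36%:

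n = [1.960·√(2 × 0.455 × 0.545) + 0.842·√(0.55 × 0.45 + 0.36 × 0.64)]² / 0.19² = 106.6, so 107 per group. The software table shows 108, a trivial difference. Then 216 × 1.3 = 280.8, rounded to 281, and 281/0.8 = 351.25, so 351. The sample size is reproduced, and the point does not depend on it.

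**2. What the design effect implies about clinics.** With 281/4, about 70 women per clinic, ICC = 0.3/69 = 0.0043. Suppose all between-clinic variance lay between urban and suburban clinics, and non-intention centred on 55% (assumed). The implied gap is 2·√(0.00435 × 0.55 × 0.45) = 0.066, or 6.6 points. Conversely, a 20-point gap means ICC = 0.01/0.2475 = 0.040 and a design effect of about 3.8. A 30-point gap means 0.0225/0.2475 = 0.091 and about 7.3.

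**3. Urban-suburban route.** The Protocol gives no clinic figures, so the gaps are assumptions. Low-income share is centred on 45% and control-condition non-intention on 55%. The programme odds ratio for non-intention is (0.45/0.55)/(0.64/0.36) = 0.46. Income has no effect within any clinic.

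Worked case, both gaps 20 points:
- Non-intention in urban clinics is 45.0% (control) and 27.3% (intervention), mean 36.2%. In suburban clinics it is 65.0% and 46.1%, mean 55.5%.
- Low-income women (35% of urban, 55% of suburban attenders): (0.35 × 0.362 + 0.55 × 0.555)/0.90 = 0.480.
- Other women: (0.65 × 0.362 + 0.45 × 0.555)/1.10 = 0.441.
- Pooled odds ratio = (0.480/0.520)/(0.441/0.559) = 1.17, although every within-clinic odds ratio is 1.

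Simulations of four clinics of 70 women, with income as the only factor (ranges are across repeat runs):

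| Gap in low-income share / non-intention (points) | Pooled OR | False positives at 0.05 |
|---|---|---|
| 10 / 10 | 1.03–1.04 | about 5% |
| 20 / 20 | 1.17–1.18 | 10–11% |
| 30 / 20 | 1.26–1.27 | 15–16% |
| 30 / 30 | 1.43–1.45 | 31–33% |

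Adding arm alone does not help here, because each arm still pools an urban and a suburban clinic (30/30: OR 1.46–1.47, 33–34%). Clinic indicators give OR 0.99–1.01 and about 5–6% throughout.

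At the 6.6-point intention gap from step 2, income gaps of 10, 20, 30 and 40 points give ORs of 1.04, 1.05, 1.08 and 1.11, with false-positive rates of 5%, 5%, 7% and 7%.

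**4. Arm route, using the planning rates.** Take 55% and 36% as proportions intending, so non-intention is 45% in the two intervention clinics and 64% in the two control clinics. Assume low-income shares of 30% and 50% respectively:
- Low income: (0.30 × 0.45 + 0.50 × 0.64)/0.80 = 0.569.
- Others: (0.70 × 0.45 + 0.50 × 0.64)/1.20 = 0.529.
- Pooled OR = (0.569/0.431)/(0.529/0.471), about 1.17.

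Shares of 20% and 60% give about 1.38. Equal shares give 1.00.

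**5. Random clinic effects, arms allocated as planned.** With low-income shares of 70/50/30/10% across clinics, the false-positive rate with no clinic or arm term is 7–8% at ICC 0 to 0.01, about 10% at 0.03 and about 13% at 0.05. With arm only it is about 5–6%, 8% and 11%. With clinic indicators it is about 4–5%.

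**The case against.** Several points on the other side stand.

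- Section 3.9(b) is silent on covariates; it does not exclude clinic. A covariate list is often left to a separate plan. It would be wrong to say that the Protocol rejects a clinic term. But 3.9 is the Protocol's own analysis plan and states a specific model. Following it as written permits the mixing, so the point is more than a missing list.
- A reader might infer from 3.1 that the clinics were picked to differ on every objective 5 factor. The text does not support that. It claims demographic similarity in the same sentence and names neither race nor age; cultural factors are the nearest to race. Income and education are the firm cases. The variability is unquantified and may lie partly within clinics.
- The larger effects need gaps of 20 to 30 points, well beyond the 6.6 points implied by the design effect. That counts against any claim that bias is certain or large. It does not settle the matter, because 3.4 gives no source for 1.3 and the planned arm shift comes on top of it.
- The simulations use one factor, while the plan is a multiple regression. Mutual adjustment could change the between-clinic component, and this was not tested.
- Objective 5 is associational, and between-clinic contrast may be wanted information. A group with lower intention overall can still be a sensible target. This is a fair point about the estimand. However, the objective names individual characteristics, and unadjusted associations can be shown alongside.
- Clinic indicators make the arm effect inestimable, and 3.9(b) is the only stated analysis of intention. This is correct and limits where the fix may be applied.

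**Conclusion.** The point holds as a possibility that the stated model leaves open. Pooled odds ratios for income and education can partly reflect clinic or arm differences. The size cannot be determined from the Protocol:

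- Negligible if clinics differ as little as a design effect of 1.3 implies (OR up to about 1.11, false positives 5–7%).
- Material if income mix and intention both differ by about 20 points or more between urban and suburban clinics (OR about 1.17, false positives about 11%, rising with wider gaps).
- Material through the arm if income mix is unbalanced between arms (OR about 1.17 at shares of 30% v 50%).

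These figures rest on assumed clinic mixes, a single-factor model and no true within-clinic effect. They do not show that objective 5 will name the wrong groups. Nor does the point reach the primary comparison: objective 5 is a secondary aim. It is a cheap improvement.

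**What to change.** In 3.9(b), state that:

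1. the objective 5 factor model includes clinic as a four-level fixed effect (three indicators), which absorbs arm and stratum, so that associations with age, race, income and education are read as within-clinic; unadjusted associations may be shown alongside;
2. this model is not used to estimate the programme effect on uptake intention, which needs its own stated analysis under objective 4.

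The first statement costs three degrees of freedom among about 281 women, and slightly wider intervals for factors that vary mainly between clinics. Clinic is known for every woman, and the sample size does not change. The second needs more than a sentence, because the Protocol gives no separate arm comparison for intention at present.
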